## Abstract

**Background:**

In developing countries, a significant number of women of reproductive age fail to meet their required intake of essential micronutrients through diet alone. Although nutrient supplementation is a common approach, it may not offer a sustainable solution, particularly in Asian countries like Sri Lanka, where healthcare is provided free from womb to tomb. Therefore, it is timely to explore nutritious and affordable local food options to enhance nutrition. *Diyabath*, a traditional meal prepared from overnight fermentation of cooked rice, is often used as a dietary therapy by indigenous medical practitioners in Sri Lanka. While the benefits of fermented foods in improving nutritional status and gut microbiome across all ages are well-known, the specific advantages of fermented cooked rice, such as *diyabath*, remain largely unexplored. This trial aims to evaluate the effects of *diyabath* on the gut microbiome, as well as on nutritional, health and immune parameters among young women of reproductive age in Sri Lanka.

**Methods:**

This is a single arm, non-randomized controlled trial among 45 women aged 20–35 years, purposively selected from a residential hostel in Colombo District, Sri Lanka. The primary outcomes: gut microbiome composition, nutritional status, and health and immune markers will be assessed before and after a 10-week control phase, during which participants will follow their usual dietary habits (control). In the subsequent 10-week intervention phase, the same participants will consume *diyabath* daily as a pre-breakfast meal (intervention). The *diyabath* will be prepared according to an optimal recipe identified through a comprehensive evaluation of traditional recipes during the intervention development phase. Outcomes will be reassessed immediately and one month after completing the intervention. Changes in outcomes between the control and intervention phases will be compared.

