### Outcomes

Outcomes will be measured at four time points: at the baseline (T_0_), after completion of the 10-week non-intervention control period (T_1_), after completion of the 10-week intervention period (T_2_) and 4 weeks after completion of the intervention (T_3_) (Fig. 3).

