**Fig. 4 Fig4:**
[figure not shown]
CONSORT flow chart for the trial

**Table 1 Tab1:** Participant timeline

Task	Study period (weeks)													
	**Recruitment**	**Non-intervention control period**						**Intervention period**					**Post-intervention follow up**	
ENROLLMENT - Eligibility screening - Informed consent	−2	0^a^	2	4	6	8	10^b^	12	14	16	18	20^b^	21	22^b^
	X													
	X													
Maintaining a food diary (24 h dietary records)		x	x	x	x	x	x	x	x	x	x	x	x	x
Baseline control assessment		x												
Anthropometry (height, weight, Waist circumference, Hip circumference, BMI)		x					x					x		x
Collection of blood samples (fasting) - serum micronutrients & serum ferritin - serum lipid profile - serum free fatty acids - AST, ALT - hsCRP, IL-6, IL-10, Cytokines - FBS & serum insulin		x					x					x		x
Collection of stool samples - Gut microbiome analysis (% abundance, alpha-diversity index, F/B ratio) - Short chain fatty acid profile		x					x					x		x

^a^assessment is done at the beginning of the week

^b^assessment is done at the last day of the week

Participants will be informed not to take part in any other nutritional intervention as well as not consume any nutritional supplementations including other cooked rice-based fermented foods during the study. A list of such food items will be given to them for reference at the beginning of the study. In addition, each participant will be asked to record daily all the foods that they have eaten other than what is provided by the hostel throughout the intervention phase. These records will be checked by an investigator during weekdays. Set reminders will be sent daily via SMS to all participants to keep records of their diets and will be asked to acknowledge the receipt of the message.

During the intervention period, every morning, the participants will be reminded via SMS to be present at the breakfast table. Standard portions of *diyabath* will be placed in the dining area before breakfast, ensuring uniformity in presentation across all participants. One investigator will be present at the site to observe the participants, to ensure that they consume *diyabath* as intended and answer any queries. The participants are requested to finish the served amounts and return the containers. If there is any leftover *diyabath*, the investigator will weigh it and make a record of it. This procedure will be repeated daily for 10 weeks during the intervention phase.

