### Statistical analysis

Data will be analysed using the statistical package for the for the Social Sciences (SPSS) version 21.0. The changes in nutritional, health and immune parameters between the baseline (T_0_) and at the end of control phase (T_1_) will be analysed first to identify any significant change with time. The end point of control phase will serve as the pre-intervention point for further assessments. The changes in outcomes between the pre-intervention point (T_1_) and at the end of intervention phase (T_2_) will be analysed to determine any significant effects of *diyabath* consumption on the study group.

Paired t-test will be performed to determine the significance of the mean difference of pre- and post- measurements during the intervention phase. *P* value less than 0.05 is considered statistically significant.$$\begin{aligned} {\mathrm H}_0=\:&\left[\mathrm{Pre}-\mathrm{intervention}\;\mathrm{measurements} -\mathrm{post}\right. \left.-\:\mathrm{intervention}\;\mathrm{measurements}\right]=0 \end{aligned}$$

The same analysis will be performed in relation to the control phase. This evaluation is important to reveal any possible change in parameters that can occur due to seasonal, physiological or climatic changes in individuals.

Further, independent sample t-test will be performed to assess the significance between the intervention and control phases, in relation to the mean change in pre- and post-measurements observed during the intervention and control phases.$$\begin{aligned} {\mathrm H}_0=\:&\left[\mathrm{Mean}\;\mathrm{change}\;\mathrm{in}\;\mathrm{control}\;\mathrm{phase} \right. \left. -\:\mathrm{Mean}\;\mathrm{change}\;\mathrm{in}\;\mathrm{intervention}\;\mathrm{phase}\right]=0 \end{aligned}$$

Bioinformatics analysis of metagenomics of microorganisms evaluated from stool samples will be carried out based on16S amplicon sequence variants (ASVs) model.

Analysis of the effect of diyabath on primary outcomes will be based on modified intention-to-treat (mITT) and per-protocol (PP) principles. The mITT population will include participants who completed the first 15 weeks of the study period which covers the control phase and half of the intervention phase. The PP population will include the participants who completely adhered to the study protocol [53]. Missing data will be adjusted with multiple imputation.

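### The published analysis section gives the scheduled post-intervention visit (T3) no role; one four-visit mixed model per outcome would use it with no new data

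*Protocol article*

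**What the plan says.** The protocol article, Outcomes, sets four measurement points. The last, T3, falls "4 weeks after completion of the intervention". The abstract agrees in substance: "Outcomes will be reassessed immediately and one month after completing the intervention". Table 1 marks anthropometry, fasting blood and stool collection in its final column, week 22. Its footnote for weeks 10, 20 and 22 reads "assessment is done at the last day of the week".

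Statistical analysis sets out the comparisons:

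- Control phase: changes "between the baseline (T_0_) and at the end of control phase (T_1_) will be analysed first to identify any significant change with time".
- Intervention phase, by paired t-test: "The changes in outcomes between the pre-intervention point (T_1_) and at the end of intervention phase (T_2_) will be analysed".
- Between phases, by an independent-samples t-test "in relation to the mean change in pre- and post-measurements observed during the intervention and control phases".

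The section also gives null hypotheses, a 0.05 significance level, two analysis populations and multiple imputation. It does not mention T3. The aim at the end of Background concerns diyabath against none and does not name persistence. Study design says only that no wash-out is considered, because the control phase comes first. No passage says that an effect would be gone by T3.

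**The concern.** With one arm and no concurrent control, a shift at T2 can come from the food or from time. Statistical analysis recognises this when it cites seasonal, physiological and climatic change as the reason for testing the control phase. T3 is the only observation taken after exposure and off the food, so it bears on whether a T2 shift reverses once diyabath stops.

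The section assigns a use to three of the four visits and none to the fourth. The list of primary outcomes is long. Any T3 comparison reported later would therefore be chosen after the data are seen, and could be chosen outcome by outcome. Participants would also give a further blood and stool sample with no published analysis attached.

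**Working it through.** **The plan's own figure.** No stated number depends on T3. The sample size formula gives (31×69 + 73×27) × 7.9 / 42² = 4110 × 7.9 / 1764 = 18.41, and doubling gives 36.82, as stated. Adding 25% gives 46.0 against the stated 45. T3 plays no part in any of these.

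**Visits against analyses.**

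| Visit | Measured | Used in a named comparison |
|---|---|---|
| T0 | yes | T0–T1; between phases |
| T1 | yes | T0–T1; T1–T2; between phases |
| T2 | yes | T1–T2; between phases |
| T3 | yes | none |

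**Assumptions for the arithmetic.** The article gives no variances or correlations. Let each reading have variance s², with correlation r between any two readings from the same woman. T0, T1 and T2 fall at weeks 0, 10 and 20, and T3 at week 24 (text) or week 22 (Table 1).

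**Between-phase contrast.** (T2 − T1) − (T1 − T0) = T2 − 2T1 + T0, with variance (1 + 4 + 1)s²(1−r) = 6s²(1−r). The independent-samples test treats the two changes as unrelated and uses 2s²(1−r) + 2s²(1−r) = 4s²(1−r). Its standard error is √(4/6) = 0.82 of the correct one. With no effect, the nominal 1.96 cut-off becomes 1.96 × 0.82 = 1.60, a two-sided error of about 11% in large samples.

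**What T3 could add to precision.** Fit linear time plus an on-diyabath term that is 1 at T2 only. The variance of that term, in units of s²(1−r), is 1 + 1/3 + (20 − m)²/S. Here m is the mean of the other three weeks and S their sum of squares about m.

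- Week 24: m = 11.33, S = 290.67; 1.333 + 75.11/290.67 = 1.592. SE ratio √(1.592/6) = 0.515.
- Week 22: m = 10.67, S = 242.67; 1.333 + 87.11/242.67 = 1.692. SE ratio √(1.692/6) = 0.531.

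This requires linear drift and no effect left at T3. Relaxing the second condition:

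- **T3 given its own effect** (as any test of persistence needs): variance 6.00, ratio 1.00, no gain.
- **Effect fully persisting, and modelled so:** variance ratio 0.997 (week 24) or 0.987 (week 22). With correlation decaying over time it is 0.86–0.96.
- **Washout assumed but wrong:** T3 has weight 1/3 + (20 − m)(24 − m)/S = 0.711 in the predicted T2 (0.769 with week 22 in place of 24). Carry-over of 25%, 50% or 100% biases the estimate by −18%, −36% or −71% at week 24, and by −19%, −38% or −77% at week 22.

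**T3 timing.** T2 and the final column are both assessed on the last day of their week, so Table 1 places the final assessment 22 − 20 = 2 weeks after T2. The text says one month or 4 weeks.

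**The case against.** The strongest objection is that this is an omission and not an error. The source is a condensed article, the statistical analysis plan is not shown, and handling of a follow-up visit could well be set there. The stated aim is answered with T0, T1 and T2. This stands in part: the supportable statement is that the published analysis section gives T3 no role, not that persistence will never be examined. It does not dispose of the point, because that section goes as far as naming visits, tests and hypotheses and passes over one of its own outcome visits.

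A reader might also infer that the plan gives up a much more precise estimate. The documents do not support that. The gain needs linear drift and full washout, and the article states neither. The washout model also assumes away the persistence that T3 would be used to examine, and it extends the equal-drift assumption to a third interval. With complete data, a model with visit as a four-level factor returns the same T2 − 2T1 + T0 contrast as T0–T2 alone.

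A further inference would be that T3 cleanly separates a food effect from a time trend. It does not. A lasting effect and a trend can both leave T3 away from T1, and a reversal could itself be seasonal.

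Finally, T3 is scheduled for all women, but it will not be obtained from every one. The article provides for withdrawal, discontinuation, and drop-out at 70% compliance or below.

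**Conclusion.** The point holds in limited form. T3 is scheduled with anthropometry, blood and stool, and enters none of the published comparisons. Persistence is not a stated aim, so no objective fails; what is available is a low-cost improvement. Reversal at T3 would support a food effect, while non-reversal would remain ambiguous between persistence and trend.

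No loss of precision is established. The 52–53% standard error holds only under equal correlation, linear drift and complete washout, and the gain vanishes when T3 has its own effect. The firmer statistical benefit of the change lies elsewhere: the between-phase contrast gets its within-woman variance, 6s²(1−r) under equal correlation, in place of the 4s²(1−r) implied by the independent-samples test. The T3 timing conflict rests on a machine-read table, so the published table should be checked.

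**What to change.** In Statistical analysis, replace the separate t-tests, including the independent-samples test on changes from the same women, by one mixed model per outcome. Visit (T0, T1, T2, T3) is a factor and woman a random effect. From it report:

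- T2 − 2T1 + T0, the between-phase contrast, as the main result;
- T3 − T2 (reversal) and T3 − T1 (persistence) as secondary contrasts. State that neither is adjusted for drift and that non-reversal cannot be attributed to the food alone.

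The linear-time fit is at most an optional sensitivity analysis, with linear drift and washout by T3 both stated as assumptions. Reconcile the timing of T3 across the abstract, Outcomes and Table 1, and describe T3 as scheduled for all women. If the analysis plan already defines a T3 analysis, refer to it here.

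The cost is wording and a modest change to the analysis code, with no new visits or samples.

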**Discussion:**

This study intends to evaluate the impact of introducing *diyabath* as a pre-breakfast meal on changes in host gut microbiome, nutritional status, and health and immune markers in young women in reproductive age. The findings may support the promotion of affordable indigenous dietary solutions, particularly in low-resourced rice-growing countries, to mitigate nutritional deficiencies and provide a basis for future research on traditional food.

**Trial registration:**

This protocol is registered in the Sri Lanka Clinical Trials Registry (SLCTR). Clinical trial number: SLCTR/2024/032 (Registration date: 09/10/2024).

## Background

Sri Lanka, a county in South Asia, has a wide variety of traditional rice and rice-based meals that link people with their rich culinary culture. This culture promotes sustainable food consumption practices, including a variety of unique preservation methods for maximum food utilization. *Diyabath* is one such traditional Sri Lankan pre-breakfast meal prepared by fermenting leftover cooked rice (from dinner) overnight, contributing to reduced food wastage. Diverse communities in Sri Lanka enhance the gastronomic value of *diyabath* by adding different ingredients such as chilies, onions and coconut milk at different stages of fermentation. This flavour infusion is a practice that not only improves the sensory quality but also adds nutritional and medicinal value. Therefore, there are different recipes of *diyabath* consumed by Sri Lankans since many decades. *Diyabath* is also used by Sri Lankan indigenous medical practitioners as a dietary remedy for conditions like gastritis and anaemia [1, 2].

In recent years, the consumption of fermented foods containing live microorganisms has emerged as an important dietary strategy for improving human health [3]. Fermentation of cereals and grains is shown to reduce the phytate activity leading to better absorption of vital minerals such as iron and zinc in the gut, and thereby enhance the bioavailability of protein [3, 4]. Further, it could produce certain desirable micronutrients such as vitamin B_12_ [5, 6]. In terms of health benefits, studies have shown positive outcomes upon consumption of fermented food in apparently healthy adults. A randomized interventional study reported enhancement of the gut health and immune parameters following a 17-week high-fermented-food diet [7], while another showed enhanced glucose metabolism following the consumption of sourdough bread (an Egyptian fermented food) [8].

A review on rice-based fermented foods showed that rice fermentation appears to be a potent tool in filling the nutritional gaps and enhancing global health. Rice fermentation is driven by the endogenous microorganisms as a natural fermentation, except for the rice-based alcoholic beverages such as *sake*. Fermentation of rice is primarily lead by lactic acid bacteria (LAB) such as *Lactobacillus bulgaricus*, *L. casei, Pediococcus acidilactici, Streptococcus faecalis, S. thermophilus* and *Saccharomyces* species, which help restore healthy intestinal flora [9]. Studies confirm that many of these LAB strains are probiotic candidates. Further, LAB produce antioxidants including active phenolic metabolites in fermented food. This blend of antioxidants and probiotics in rice-based fermented foods reveals their health benefits as functional food. Moreover, rice fermentation also yields compounds such as organic acids and amino acids including essential ones [10]. Germinated brown rice fermentation has shown anti-inflammatory properties due to the increase in its composition of bioactive compounds [11]. *Idli* is a traditional Indian food prepared from the fermentation of rice and black gram (lentil) as its main ingredients. The microbiome analysis of *idli* has revealed that the endogenous microorganisms present in *idli* produce short-chain fatty acids such as butanoate and propanoate. These fatty acids aid in lowering the pH and thereby enhance the bioavailability of minerals as well as inhibiting the harmful bacteria in the gut [12]. Thilagavathi et al. (2019) showed that the fermented cooked rice water is a good source of natural compounds with antimicrobial, antioxidant and anticancer activities. In addition to that, via an in-vitro assay, they claim that it effectively hinders the proliferation of hepatocellular carcinoma cells [13]. Further, *basi*, a fermented cooked rice preparation which is consumed as breakfast since many decades by ethnic people of Madhya Pradesh of India is also considered as a highly nutritious food. This is prepared by natural fermentation of cooked rice by soaking the cooked rice in water in an earthenware pot, hence very similar to *diyabath* [14]. According to Tiwari *et* al. (2019), the consumption of *basi* provides sufficient amount of essential nutrients such as iron, zinc, copper, manganese and potassium that may help cure blood disorder like anemia, improves malnutrition, enhance bone growth and muscle formation and reduces the chances of occurrence of diarrhea [14]. Therefore, *diyabath* can also be considered as a potential food to enhance health.

A Sri Lankan study reports that a *diyabath*-based spread contains good amounts of protein (5.2 ± 0.08%), polyunsaturated fatty acids (i.e. Linoleic acid: 9.74%) and micronutrients such as Vitamin B_12_ (2.3 µg/100 g)_,_ Iron (64.25 mg/100 g), Zinc (9.74 mg/100 g), Mg (167.79 mg/100 g) and Ca (184.94 mg/100 g) [15]. Two Sri Lankan reviews claim that *diyabath* is considered as a remedy for gastritis and also to reduce blood glucose levels due to its low glycaemic index [16, 17]. Further, according to Jayawardena and Wansapala (2015), *diyabath* contained *Lactobacillus* group bacteria at the end of 12 h fermentation period [15].

To achieve a holistic understanding of this traditional *diyabath* preparation in Sri Lanka, a multi-pronged approach was implemented (Fig. 1). Examination of traditional medicine scripts and the Ayurvedic pharmacopeia was followed by conducting archival scoping review to explore historical insight. Further, a systematic literature review was conducted to integrate current scientific knowledge on the functional and health benefits of fermented rice. A community survey was also conducted to gather traditional knowledge on *diyabath* preparation methods [18]. Potential participants for the survey were recruited purposively from all administrative provinces in Sri Lanka. The identified recipes were shortlisted via a panel discussion according to the modified Delphi technique [19]. The three shortlisted recipes were then prepared according to the developed standard operational procedures (SOP) and evaluated in view of its nutritional composition, microbiological and chemical safety and palatability. The results of the microbiological assays were compared with the recommended limits in the SLSI and regional standards such as FASSAI (Indian standard) and confirmed the microbial safety of *diyabath* [20–22]. Further, mineral analysis didn’t detect heavy metals in *diyabath*, therefore, is safe for the consumption.

**Fig. 1 Fig1:**
[figure not shown]
Flow of the intervention development

According to our preliminary analysis, *diyabath* is rich in iron, magnesium, manganese and copper (with up to 15%, 8.78%, 19.6% and 31.1% of contribution respectively to the daily recommended value of each element per one serving of diyabath; one cup-230 g). The antioxidant activity in *diyabath* is high and comparable to other antioxidant-rich foods. The LAB count is in the range of 10^6^ CFU/g, making it a potential source of probiotic. Furthermore, the addition of red onions, roasted red chili and coconut milk for flavour infusion can also exert a prebiotic action as proven in previous studies [4, 9, 23–25]. Therefore, collectively, *diyabath* can serve as a beneficial ‘symbiosis’ that will enrich the gut microbiome. *Diyabath* made from different rice varieties were also tested for their sensory properties according to ISO 13299 [26]. Since *diyabath* made from parboiled *nadu* rice (Sri Lankan rice variety Bg 352) scored more for taste, it was selected for further investigations, thus prepare the intervention. Parboiling is a traditional post-harvest processing method of rice practiced in South Asia which consists of steeping the paddy in hot water, continuing to steam and then drying the steamed rice down to an appropriate moisture [27]. A Sri Lankan randomized cross over study using healthy volunteers concluded that the glycaemic index of *nadu* (Bg 352) is low (40 ± 4). Therefore, it has been recommended that, parboiled *nadu* is of nutritional significance to the individuals who are concerned on controlling their energy intake and glycaemic response [28]. The above results from our preliminary study and the closely related other studies assure that *diyabath* can improve gut microbiome as well as nutritional, health and immune parameters in human. However, there is limited published literature of scientifically evaluated data on the nutritional, immune and health impact of consuming *diyabath* or similar fermented rice-based foods, which will be accomplished via this clinical trial.

Micronutrient deficiencies, especially anaemia, are common among Asian women of reproductive age [29]. The World Health Organization (WHO) reports that 48% of pregnant women in such countries are anaemic [30]. Although most Sri Lankan pregnant women meet their recommended energy intake, they often fall short of essential micronutrients such as iron, zinc, folic acid and vitamins D, A and B_12_ through their diet [31, 32]. Recently, 29.1% of first trimester pregnant women were found to be anaemic, highlighting the inadequate pre-pregnant serum iron status of women in Sri Lanka [33]. This issue has been aggravated by the COVID-19 pandemic and economic downturns, leading to disrupted food supplies and poor affordability. Although nutrition supplementation programmes that target pregnant women are available in Sri Lanka, they may not be sustainable in a country that provides free healthcare from womb to tomb. In this context, evaluating low-cost, domestically prepared, yet nutritious food is a viable option to improve the nutrition of reproductive women in Asia. In particular, this intervention has the potential to benefit young women, who represent the primary age group for first-time pregnancies in Sri Lanka [34]. By improving their nutritional status and gut health, they may be better prepared to minimize complications during pregnancy [35]. Such an approach aligns well with the Sustainable Development Goals (SGD).

Studying the long-term benefits of *diyabath* could prove useful. As a dietary solution based on rice, which is the staple in most Asian countries, *diyabath* could economically address women’s nutrition, and thereby maternal and child health more effectively than food fortification or supplementation. It would be a feasible option as it can be prepared by overnight fermentation of leftover cooked rice without additional cooking, making it convenient for people with busy lifestyles. It is also a plausible solution to minimise food waste in Sri Lanka, where half of the biodegradable municipal solid waste is due to food waste [36, 37]. The findings of this study could also be adopted by other Asian countries with similar socio-cultural backgrounds and rice production; and contribute positively to ‘sustainable consumption’ in response to current food crises in the world.

The study aims to evaluate the changes in host gut microbiome composition upon *diyabath,* a traditional rice-based fermented pre-breakfast meal vs none (only the regular breakfast) in relation to host nutritional status, health biomarkers and immune parameters of young women of reproductive age in Sri Lanka.

